### Inclusion Criteria

1. Preterm babies less than 29 weeks ELGAN.
2. Babies born in RAH and admitted to RAH NICU for first 7 days of life.

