### Exclusion Criteria:

1. Structural heart diseases.
2. Major congenital disorder or chromosomal disorder.

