### Study Procedure:

This will be a Non-Blind Randomized Control Trial.

The study will involve the following steps ([APPENDIX 1](#)):

- 1) The study population will be assigned by simple randomization to either Multimodal arm to receive multimodal hemodynamic assessment using the study guideline ([APPENDIX 5](#)) or Standard arm to be treated according to the standard approach operative in RAH NICU.

- 2) ELGANs recruited into Standard arm will have
  - a) Continuous cardiorespiratory monitoring using ECG leads or via an Arterial line, and pulse oximetry and intermittent non-invasive blood pressure monitoring as standard of care in the NICU. Continuous arterial blood pressure monitoring will also be obtained as appropriate when an arterial line has been placed under the clinical team's discretion.
  - b) TNE studies will be performed at the discretion of clinical team for concerns on cardiorespiratory status of the study population.
  - c) The current treatment protocol for hemodynamic compromise at our NICU is starting inotropic support if mean blood pressure (MBP) is less than the gestational age of the infant in the first 72 hours of life.
  - d) Cerebral NIRS monitoring for rScO2 using neonatal sensors is not routinely used in the NICU and its application for the standard arm will be up to clinical team discretion.
- 3) ELGANs recruited to the Multimodal arm will have the same monitoring outlined in 2a in a standardized manner.
  - a) Continuous cerebral NIRS monitoring for rScO2 using neonatal sensor will be attached to the forehead of the infant for first 72 hours of life ([APPENDIX 2](#)).
  - b) Hemodynamic assessment using TNE ([APPENDIX 3](#)) will be performed at 18-24 hours and 66-72 hours of life. Additional TNE studies will be performed at the discretion of the clinical team for concerns on cardiorespiratory status of the study population.
  - c) Zubrow's Normative BP chart will be used and MBP less than the third centile for the gestational age will be taken as low BP for the study.
  - d) Blood pressure values and NIRS data will be integrated along with the clinical/biochemical information every 6 hours as well as whenever there is a deviation from the normal range.
  - e) A comprehensive study guideline comprising of the clinical, biochemical and NIRS data will be used by the study team in such cases to derive to the hemodynamic assessment of the study subject.

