## Data Management:

### Data Collection and Handling

Case report forms will be devised to aid data collection. The following patient demographics will be recorded: gestation, birth weight, type of pregnancy, type of delivery, antenatal morbidities (PIH, placental abruption, chorioamnionitis), antenatal steroids, antenatal MgSO4, Apgar Scores, and gender. Information will be collected about the active clinical issue and disease states at the time of the hemodynamic assessment. Data pertaining to cardiorespiratory support, ventilation requirement, inotropes requirement will be recorded during the first week of life. Data for the TNE cardiac function

studies will be collected in a separate datasheet and continuous NIRS data will be collected for the first 72 hours of life. Major morbidity data like BPD, NEC, ROP, severe brain injury, PDA and mortality will be collected for the purpose of validation of VVR Score in the transitional neonatal period. All data will be entered into REDCap Software and will be securely stored on an institutional computer that is password protected.

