## Statistical Plan and Data Analysis:

### Sample Size Calculation for VVR Scores

Assuming 25% reduction in VVR in intervention arm with mean VVR Score of 30 in control arm and 22.5 in intervention arm, sd-15; t test assuming  $sd_1 = sd_2 = sd$ ;  $H_0: m_2 = m_1$  versus  $H_a: m_2 \neq m_1$

Study Parameters:

$\alpha = 0.0500$ ;  $\text{power} = 0.8000$ ;  $\text{delta} = -7.5000$ ;  $m_1 = 30.0000$ ;  $m_2 = 22.5000$

$sd = 15.0000$

Estimated sample sizes:  $N = 128$ ;  $N \text{ per group} = 64$

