### Analysis

All statistical analyses will be performed with the intercooled Stata Version 18.0 (College Station, Texas). All data will be anonymized for analysis and intention to treat analyses will be performed for primary outcome. All the tests will be two-sided (where applicable), and significance will be defined as p-value  $< 0.05$ . Univariate and bivariate analysis will be done to describe the sample. Categorical variables will be compared by Fisher's Exact Test and continuous variables by Student's t-test (two-sided). Logistic and linear regression models will be developed using forward and backward stepwise methods to examine the association between different VVR cut off (95th centile for the entire study cohort and literature derived cut off of  $VVR > 53^{25}$  that is associated with adverse outcomes in neonatal postoperative cardiac patients) and neonatal outcome. ROC curve will be used for the purpose of validation of the VVR Scores in neonates during the neonatal period.

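### The protocol does not say how siblings from multiple births are allocated, and its analyses treat every infant as independent; the effect is small if infants are randomised singly, larger if siblings share an arm

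*Protocol*

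**What the plan says.** Inclusion Criteria admits "Preterm babies less than 29 weeks ELGAN" who are born at the site. Exclusion Criteria has two entries, structural heart disease and "Major congenital disorder or chromosomal disorder". Neither removes twins or triplets, so their eligibility follows from the absence of an exclusion.

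Data Collection and Handling lists, among the baseline items, "gestation, birth weight, type of pregnancy, type of delivery". The third item is not defined. Multiplicity is its natural reading, but nothing in the analysis uses it.

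Study Procedure, item 1, gives the allocation method: "The study population will be assigned by simple randomization to either Multimodal arm" or the standard arm. It does not say whether siblings receive separate, shared or opposite assignments.

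The Analysis section compares "continuous variables by Student's t-test (two-sided" and categorical variables by Fisher's exact test. It adds stepwise logistic and linear regressions linking VVR cut-offs to neonatal outcome, and an ROC curve. The sample size section counts 128 independent observations.

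**The concern.** Siblings share their gestation and much of their antenatal history, including steroid exposure and chorioamnionitis, which the protocol itself records as baseline factors. Their day-7 VVR scores and morbidities are therefore likely to be correlated. The named tests assume that they are not.

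The consequence depends on a rule that the protocol does not give. If siblings share an arm, the t-test's standard error is too small. If each infant is randomised separately, the test is sound on average but leaves some information unused. The regressions and ROC analysis that serve the secondary objective (validating VVR) pool infants across arms, so randomising infants singly does not remove the correlation there.

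**Working it through.** **Reproducing the plan's figure.** Inputs from Sample Size Calculation: means 30 and 22.5, SD 15, two-sided alpha 0.05, power 0.80. The normal approximation gives 2 × (1.960 + 0.842)² × (15/7.5)² = 62.8, so 63 per arm. The exact t calculation gives power 79.5% at 63 and 80.1% at 64 per arm. The stated 64 per group (N = 128) is reproduced, for independent infants.

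**Assumptions not in the documents.** f is the share of infants who belong to twin pairs, taken as 0.2-0.3. rho is the within-pair correlation of VVR, taken as 0.3-0.7. Triplets are left out; kept together, they would raise the design effect further.

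**Case 1: each infant randomised separately.** On average half the pairs share an arm (adding f·rho/2 to the variance factor) and half are split (subtracting f·rho/2), so the net factor is 1. A simulation of the plain t-test at N = 128 (40,000 trials per setting; f 0.25-0.4, rho 0.3-0.9) gave type I error 4.8-5.3% and power about 80% at the planned effect.

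Information available from modelling the pairs, relative to the t-test: a shared pair carries 1/(1 + rho) and a split pair 1/(1 − rho), which average to 1/(1 − rho²). The overall gain is (1 − f) + f/(1 − rho²).

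| f | rho = 0.3 | rho = 0.5 |
|---|---|---|
| 0.2 | 0.8 + 0.2/0.91 = 1.02 | 0.8 + 0.2/0.75 = 1.07 |
| 0.3 | 0.7 + 0.3/0.91 = 1.03 | 0.7 + 0.3/0.75 = 1.10 |

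The gain is thus 2-10%. These are upper bounds at those values, because rho would have to be estimated from about 13-19 pairs (0.2 × 128/2 = 12.8; 0.3 × 128/2 = 19.2).

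**Case 2: siblings assigned together.** Design effect DE = 1 + f·rho. True alpha of the plain test = 2 × [1 − Φ(1.96/√DE)].

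- f = 0.2, rho = 0.3: DE = 1.06, alpha = 5.7%.
- f = 0.3, rho = 0.5: DE = 1.15, alpha = 6.8%. With a clustered analysis, power at N = 128 is about 75%, and 128 × 1.15 = 147.2, so 148 infants are needed.
- f = 0.3, rho = 0.7: DE = 1.21, alpha = 7.5%.

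**Case 3: siblings deliberately split.** DE = 1 − f·rho. Over the same range alpha is 2.7-4.3%, so the plain test is conservative.

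**VVR-outcome regressions, with siblings pooled across arms.** Take f = 0.3 and a sibling correlation of 0.5 for both VVR and outcome. The variance factor is 1 + 0.3 × 0.5 × 0.5 = 1.075. The naive variance is 1 − 1/1.075 = 7.0% too small, and the standard error 1 − 1/√1.075 = about 3.6% too small.

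**The case against.** The strongest reply is that the primary test is valid under the only allocation method the protocol states. A reader might infer that the trial has an inflated false-positive rate. The documents do not support that: no passage puts siblings in the same arm, and infant-by-infant randomisation leaves alpha near 5%. This part of the reply stands, and the inflation must be read as conditional.

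A reader might also infer that ignoring the pairing discards the trial's most precise comparison. That is wrong. With 20-30% twins, simple randomization yields about 6-10 split pairs. With SD 15, the standard error of the within-pair contrast is √(2 × 15² × (1 − rho)/pairs). This runs from √(450 × 0.3/9.6) = 3.8 to √(450 × 0.7/6.4) = 7.0, against 15 × √(2/64) = 2.65 for the ordinary comparison.

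Three further replies have some force:

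- **Model choice.** VIS is zero without vasoactive support and VI is zero on CPAP (Appendix 4), so a normal random-intercept model is not plainly superior. The t-test faces the same distribution, and clustered standard errors are an alternative.
- **ROC.** The protocol specifies no confidence interval for the ROC curve, so there is no stated interval to call too narrow. The point applies only if one is reported.
- **Detail left to the SAP.** Anonymising the data does not rule out a coded family link, and a SAP could add a model. But the protocol already names the tests, and the allocation rule has to be settled before the first multiple pregnancy is randomised.

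**Conclusion.** The point holds as a modest one. The protocol admits multiples, omits their allocation rule, and fixes analyses that ignore the correlation between siblings.

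Under separate randomisation of each infant, the primary t-test is sound, and the loss is at most about 2-10% of information at correlation 0.3-0.5. Assigning siblings together would raise type I error to about 5.7-7.5% and leave the trial short of 80% power under a proper clustered analysis. The VVR-outcome regressions are slightly too confident under either rule.

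The directions follow from the design. The sizes rest on assumed shares of twins and assumed correlations, and shrink towards nothing if few multiples enrol.

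**What to change.** 1. In Study Procedure, state that siblings are randomised individually. If they are to share an arm, say so, require a clustered analysis and revisit the sample size.
2. Keep a coded pregnancy identifier in the REDCap export used for analysis.
3. Analyse day-7 VVR with a random intercept for pregnancy (with small-sample degrees of freedom) or with standard errors clustered on pregnancy. Clustered errors around the simple difference in means protect the error rate but do not recover the precision gain.
4. Cluster on pregnancy in the VVR-outcome regressions. If an interval for the area under the ROC curve is reported, obtain it by resampling pregnancies.

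The cost is one data field, a few sentences and a slightly more complex model. With few multiples the result will be close to the t-test.

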### Secondary Objective

To validate the use of VVR Scores during the neonatal transition period in ELGAN population.

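### The stepwise regressions on VVR split at the 95th centile or at 53 rest on about 5 to 7 of 128 infants and are too sparse to add much to the validation of the score

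*Protocol*

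**What the plan says.** The protocol has one secondary objective: "To validate the use of VVR Scores during the neonatal transition period in ELGAN population". The Data Collection and Handling section says that BPD, NEC, ROP, severe brain injury, PDA and mortality are recorded for this validation.

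The Analysis section then names two analyses.

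- **Regression.** "Logistic and linear regression models will be developed using forward and backward stepwise methods to examine the association between different VVR cut off" and neonatal outcome. The cut-offs are the "95th centile for the entire study cohort and literature derived cut off of" VVR above 53, the latter being one "that is associated with adverse outcomes in neonatal postoperative cardiac patients) and neonatal outcome".
- **ROC curve.** The next sentence plans a ROC curve for validating the score. It is not tied to either cut-off.

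The sample size of 128 (64 per arm) is set only for the difference in mean VVR: "Assuming 25% reduction in VVR in intervention arm with mean VVR Score of 30 in control arm and 22.5 in intervention arm, sd-15". The protocol gives no expected number of infants above a cut-off and no outcome rates.

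**The concern.** A cut at the 95th centile puts about one infant in twenty in the exposed group, whatever the data look like. In a cohort of 128 that is a handful. The second cut-off lies far in the upper tail of the distribution assumed for the sample size, so it does much the same.

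A logistic model whose main predictor is present in about six infants gives wide intervals, and an odds ratio can move a long way on the outcomes of two or three of them. Choosing covariates by forward and backward selection in the same data adds to this: the retained terms have p-values that are too small and odds ratios biased away from the null. The regression part could therefore report an association, or none, largely by chance, and the information in VVR below the cut would go unused in those models.

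**Working it through.** **Inputs from the protocol.** Means 30 and 22.5, SD 15, 64 per arm, two-sided alpha 0.05, power 0.80 (Sample Size Calculation for VVR Scores); cut-offs at the cohort's 95th centile and at 53 (Analysis). Outcome rates, odds ratios, risks and AUC values below are assumptions, because the protocol gives none.

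**1. The plan's own figure.** Standardised difference = 7.5/15 = 0.5. The noncentral t calculation gives 63.8, so 64 per arm and N = 128 (power 0.801). The stated size reproduces.

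**2. Infants above the 95th centile.** 0.05 × 128 = 6.4, so 6 or 7, depending on how the centile is computed.

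**3. Infants above 53, normal model.**
- Control: P(Z > (53 − 30)/15) = P(Z > 1.533) = 0.0626; × 64 = 4.0
- Multimodal: P(Z > (53 − 22.5)/15) = P(Z > 2.033) = 0.0210; × 64 = 1.3
- Total about 5.4

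Sensitivity of this count:

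| Assumption | Infants above 53 |
|---|---|
| Normal, means 30 and 22.5 | 5.4 |
| Gamma, same means and SD | 7.8 |
| Lognormal, same means and SD | 7.5 |
| Normal, both arms at 30 | 8.0 |
| Normal, both arms at 22.5 | 2.7 |

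**4. Overlap of the two cuts.** Solving 0.5 × P(N(30,15) > c) + 0.5 × P(N(22.5,15) > c) = 0.05 gives c = 51.7, close to 53. The two cut-offs are nearly one analysis done twice.

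**5. Precision of the cut-off comparison.** Exact power of Fisher's test, 6 infants above the cut and 122 below:

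| Outcome rate below the cut | OR 3 | OR 5 | OR 10 |
|---|---|---|---|
| 10% | 17% | 36% | 69% |
| 20% | 23% | 45% | 76% |
| 40% | 20% | 36% | 59% |

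For an assumed risk of 60% above the cut and 30% below, power is 28%, 28% and 36% with 5, 6 and 7 infants above it.

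**6. Ceiling on sensitivity.** Even if all 6 infants above the cut had the outcome, sensitivity could not exceed 6/13 = 46%, 6/26 = 23% or 6/51 = 12% at overall prevalence of about 10%, 20% or 40%.

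**7. Cost of splitting the score.** Simulated cohorts with the protocol's means and SD, assuming that log-odds rise by 0.6 per 15 points and about 30% of infants have the outcome: power is about 86% with VVR continuous, 36% at the 95th centile and 28% at 53. This is one scenario, shown for the contrast.

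**8. What the planned ROC curve can deliver.** With n1 infants with and n0 without the outcome, the Hanley–McNeil variance is [A(1 − A) + (n1 − 1)(A/(2 − A) − A²) + (n0 − 1)(2A²/(1 + A) − A²)]/(n1 × n0). For A = 0.75, n1 = 26, n0 = 102: (0.1875 + 25 × 0.0375 + 101 × 0.0804)/2652 = 0.00348, so SE = 0.059 and the 95% half-width is 1.96 × 0.059 = 0.12. At prevalence of 10% and 40% the half-widths are 0.16 and 0.09. Power against an AUC of 0.5 is 85%, 98% and above 99% at prevalence of 10%, 20% and 40%.

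**The case against.** The strongest reply is that validation does not hang on the cut-off models. The Analysis section uses them to examine association and gives validation to the ROC curve, which uses the whole score and every infant. Step 8 shows that this curve is reasonably informative at N = 128. This stands. A reader might infer from the sparse cut-offs that the secondary objective cannot be met as written; the protocol does not support that.

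Three further points reduce the concern without removing it.

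- **The 95th centile is set in the same infants it is used on.** A reader might see this as circular. But the centile depends only on the VVR distribution and not on outcomes, so it lacks the optimism of a cut-off tuned to outcome. What remains is that it may not carry over to another cohort.
- **Separation.** A reader might expect the logistic models to break down outright. In an unadjusted model with 6 infants above the cut at 60% risk, all or none have the outcome with probability 0.6⁶ + 0.4⁶ = about 5%. Over odds ratios of 3 to 5 and outcome rates of 10% to 40% it is about 4% to 21%. That is a real risk, not a certainty, and the planned linear models do not separate at all.
- **The count above 53 is model-dependent.** The normal inputs imply 64 × (0.0228 + 0.0668) = 5.7 infants with a score below zero, which is not realistic for this score, and the inputs size the 7-day score only. Hence the range of 3 to 8 in place of a single figure. No value in that range supports a multivariable stepwise model.

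Testing whether a published cut-off carries over is also a legitimate question. It can be answered descriptively.

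**Conclusion.** The point holds for the cut-off regressions only. They would compare about 6 or 7 infants with the rest at the 95th centile, or about 5 (roughly 3 to 8) at 53, and under the plan's inputs these are nearly the same infants. Power stays below one half for odds ratios up to 5 over the outcome rates tried, and reaches 59% to 76% only at an odds ratio of 10. Stepwise selection, which the protocol states outright and does not leave open, makes the results less trustworthy still.

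The 95th-centile count needs only N = 128. The count at 53 rests on the planning means and SD and on the shape of the distribution; the power figures rest on assumed outcome rates and effects. The primary analysis is unaffected, and the secondary objective can still be addressed through the ROC curve. This is a cheap improvement to one part of a secondary analysis.

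**What to change.** In the Analysis section:

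1. Replace the stepwise cut-off models with regression on VVR as a continuous predictor and a small prespecified covariate set, for example gestation, sex and arm.
2. State that the planned ROC analysis, reported as the AUC with its confidence interval, is the main validation result.
3. Report the cut-off of 53, and the 95th centile if it is kept, only as a descriptive table of sensitivity and specificity.

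The functional form of VVR and any internal validation of the AUC can be left to the statistical analysis plan. The change is to wording only and needs no extra infants or data. The downside is that no cut-off is tested formally.

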  - f) The findings will be carefully integrated within the clinical context to reach a description of the hemodynamic status of the study infant ([APPENDIX 5 and 7](#)).
- 4) All neonates will have standardized assessment for lead related skin abrasions as per standard practice, neonatal pain and stress assessment (NPASS Score) as part of their standard care.
- 5) Developmental support care will be given by the support person during the TNE assessment as per standard unit practice.

- 6) The discontinuation of either or both NIRS and TNE will depend on the discretion of the clinical team. The reason for the discontinuation will be sorted. This does not constitute a deviation from the study protocol.
- 7) The admission, 24 hours, 48 hours, 72 hours and 7days mean and median VVR and VIS scores will be calculated in both Study and Standard arms. ([APPENDIX 4](#)).
- 8) Urine output will be monitored during the study period as a surrogate for renal function and urine output less than 1 ml/kg/hr will be considered as oliguria.
- 9) SNAPPE-II Scores, which is a validated disease severity score in preterm babies, will be calculated in both study and standard arm at admission, 72 hours and 7 days of life.
- 10) The study team will be available 24/7 for hemodynamic consultation and for the ease of making hemodynamic interpretation, each pathway in the comprehensive guidelines will be transcribed into individual flash cards that will be easily accessible to study team. ([APPENDIX 8](#)).

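### VVR is validated by an unadjusted ROC curve and stepwise cut-off regressions, with no benchmark and no covariate forced in, so its AUC cannot be told apart from the effect of immaturity

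*Protocol*

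**What the plan says.** The Protocol has one secondary objective: "To validate the use of VVR Scores during the neonatal transition period in ELGAN population". Data Collection and Handling names the outcomes: "Major morbidity data like BPD, NEC, ROP, severe brain injury, PDA and mortality will be collected for the purpose of validation of VVR Score".

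The Analysis section gives two tools.

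- Regression: "Logistic and linear regression models will be developed using forward and backward stepwise methods to examine the association between different VVR cut off" and neonatal outcome. The cut-offs are the cohort's own 95th centile and a value above 53 taken from neonatal cardiac surgery. No adjustment covariate is listed.
- ROC: "ROC curve will be used for the purpose of validation of the VVR Scores in neonates during the neonatal period". No reference score or model, outcome, VVR time point or AUC regarded as adequate is given.

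The data for a benchmark are already collected. Data Collection and Handling records "gestation, birth weight, type of pregnancy, type of delivery" and other birth variables. Study Procedure, item 9, states that "SNAPPE-II Scores, which is a validated disease severity score in preterm babies, will be calculated in both study and standard arm at admission", and again at 72 hours and 7 days. Item 7 calculates VVR at those three times and also at 24 and 48 hours. The Analysis section does not mention SNAPPE-II.

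**The concern.** VVR is built from inotrope doses, ventilator settings, PaCO2 and the rise in creatinine (Appendix 4). It is reasonable to assume that less mature infants need more of this support and also have more BPD, NEC, ROP, brain injury and death. VVR would then discriminate these outcomes even if it held no information beyond immaturity. An unadjusted AUC cannot separate the two explanations.

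The Background says that no neonatal study has used VVR in the transitional period, so this analysis may become the reference for later use of the score. VVR at 7 days is also the primary outcome, and a validation claim that says more than the analysis shows would lend the primary result weight it has not earned.

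**Working it through.** **1. The Protocol's own figure.** The only sample size given is for the difference in mean VVR: 30 against 22.5, SD 15, two-sided alpha 0.05, power 0.80. The standardised difference is 7.5/15 = 0.5. The t-test solution is 63.8 per group, hence 64 per group and 128 in total, as stated. No size is given for the validation objective, so N = 128 is used below.

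**2. Can the cut-off regressions carry the validation?**
- Above the 95th centile: 0.05 × 128 = 6.4 infants.
- Above 53, assuming normal scores with the planning means and SD:
  - control: z = (53 − 30)/15 = 1.53, upper tail 0.063, × 64 = 4.0 infants;
  - intervention: z = (53 − 22.5)/15 = 2.03, upper tail 0.021, × 64 = 1.3 infants.

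Only about 5 to 6 infants would exceed either cut-off. The stepwise procedure also need not retain gestation.

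**3. What does an unadjusted ROC show for a score that adds nothing?** The Protocol gives none of the inputs needed, so these are assumptions: event rate 10, 20 or 40%; AUC of gestational risk 0.70, 0.75 or 0.80; correlation r of VVR with that risk 0.3, 0.5 or 0.7. Model:
- outcome y drawn at the event rate; gestational risk g = Normal(0,1) + d·y, with d = √2 × Φ⁻¹(AUC of gestation);
- VVR = r·g* + √(1 − r²) × noise, where g* is standardised g. VVR is therefore independent of the outcome once g is known.

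There were 3,000 trials per cell. The adjusted test is a likelihood-ratio test of VVR after g in logistic regression, on 600 trials per cell.

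| Events, gestation AUC | r | Mean VVR AUC | 95% CI above 0.5 | AUC ≥ 0.70 | VVR significant after gestation |
|---|---|---|---|---|---|
| 10%, 0.70 | 0.3 | 0.563 | 14% | 5.6% | 4.8% |
| 10%, 0.70 | 0.7 | 0.642 | 42% | 25% | 5.5% |
| 20%, 0.75 | 0.3 | 0.575 | 23% | 2.4% | 4.8% |
| 20%, 0.75 | 0.5 | 0.626 | 52% | 11% | 6.3% |
| 20%, 0.75 | 0.7 | 0.676 | 81% | 36% | 4.7% |
| 40%, 0.80 | 0.3 | 0.589 | 40% | 2.0% | 6.2% |
| 40%, 0.80 | 0.7 | 0.707 | 99% | 58% | 3.7% |

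Over all 27 cells the ranges are 14-99% (interval above 0.5), 0.3-61% (AUC at least 0.70) and 3.7-7.2% (adjusted test).

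A second simulation used a logistic outcome model with 30% events, gestation AUC 0.70-0.79 and a Mann-Whitney test at p < 0.05. It gave 45-96% at r = 0.5-0.7 and about a fifth to a third at r = 0.3.

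**4. Should a significant adjusted test be required?** Assume 30% events (0.30 × 128 = 38.4) and a true adjusted odds ratio of 1.5 per SD of VVR. Then SE ≈ 1/√[128 × 0.3 × 0.7 × (1 − R²)], where R² is the share of VVR variance explained by the covariates.
- R² = 0.25: SE = 0.223, z = 0.405/0.223 = 1.82, power ≈ Φ(1.82 − 1.96) = 44%.
- R² = 0.50: SE = 0.273, z = 0.405/0.273 = 1.49, power ≈ Φ(1.49 − 1.96) = 32%.

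Such a rule would refuse a genuinely informative score more often than not.

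**The case against.** Five points can be made for the plan.

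- **Regression is planned too.** A reader might infer that the ROC curve is the whole validation. It is not: the preceding sentence plans regressions, and stepwise selection implies candidate covariates. This stands against the word alone, but it does not cure the problem. No covariate is named or kept by rule, and the models use cut-offs that few infants exceed.
- **No rule for validity is stated.** A reader might infer that a worthless score would often be declared valid. The documents do not support this. They nowhere say that an AUC above 0.5 suffices, and the frequency depends on assumed inputs. Entry is limited to "Preterm babies less than 29 weeks ELGAN", which could weaken both the AUC of gestation and its correlation with VVR. The simulation also sets added value to zero and says nothing about how likely that is. All of this stands. The percentages show what the method cannot distinguish; they do not forecast the result.
- **Discrimination is one accepted meaning of validation.** This is true, and the objective does not claim that VVR beats gestation or SNAPPE-II. An unadjusted AUC is a legitimate result if it is described as such.
- **A SAP may supply the comparator.** It may. But the Protocol itself fixes a method, and that method cannot answer the wider question.
- **SNAPPE-II might be analysed.** It could fall under the general t-test sentence as a comparison between arms, so it cannot be said to go wholly unused. That sentence does not set it against VVR.

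**Conclusion.** The concern holds in this form: the stated validation has no benchmark and no forced adjustment, although suitable variables are collected in both arms. Its result therefore could not distinguish an informative VVR from a proxy for immaturity.

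The size depends on the assumptions. Weak correlation with gestation, or a demanding AUC threshold, makes a misleading result uncommon in most settings; moderate to strong correlation with an interval-above-0.5 reading makes it common. The adjusted test's rate near 5% also rests on an assumption, since the simulation adjusts for the very risk that generates the outcome; recorded gestation may capture it less completely.

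This is an inexpensive improvement to a secondary objective. The randomised comparison and its sample size are not affected.

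**What to change.** In the Analysis section:

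1. Name the outcome or outcomes and the VVR time point. Report the AUC of continuous VVR beside that of SNAPPE-II at the same time point (admission, 72 hours or 7 days) and that of gestation plus birth weight, each with the paired difference and 95% CI.
2. Fit continuous VVR in a logistic model that always contains gestation, SNAPPE-II and randomised arm. Report the adjusted odds ratio and the change in AUC with 95% CIs. Keep the cut-off regressions as descriptive.
3. Do not make a significant likelihood-ratio test a condition for validation, given power of about 32-44% in the example above. Instead, word the conclusion as unadjusted discrimination unless added value is shown.

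The cost is wording and a few analyses; no new data are needed. Intervals will be wide and the result may be less favourable. With about 38 assumed events, four model terms leave roughly 38.4/4 = 9.6 events per term. At a 10% event rate this falls to 12.8/4 = 3.2, so for rare outcomes the adjusted model will be fragile and should be read with caution.
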